### International Classification of Functioning, Disability and Health

We have chosen the outcome measures along the ICF concept, since it is a highly useful framework describing and organizing health conditions in a comprehensive way involving a biopsychological model. Furthermore, it provides a standard language and a conceptual basis for the definition and measurement of health and disability. Since the ICF was introduced by the World Health Organization (WHO) in 2001 [16], it has become the most used instrument to describe deficits of functional health conditions, disability, social impairment, and relevant environmental factors. In order to provide a global picture of the patients’ status as accurately as possible, we have chosen outcome measures from the main domains of the ICF concept (see Fig. 1):
Body function and structureActivity and participationContextual factors (composed of environmental and personal factors).

**Fig. 1 Fig1:**
[figure not shown]
Interactions between ICF components (according to WHO [16]) and associated outcome measures used in the present study

## Aim of study

The aim of the present study is to evaluate the effectiveness of the rehabilitation programs for thermal injuries at two centers in Germany. Changes in health status are measured along the ICF constructs of body function and structure, activities, participation, and contextual factors (environmental and personal factors) in order to address health issues as completely as possible. Patients’ conditions in the different domains will be measured before and after the rehabilitation and at two follow-up points, 3 and 12 months after rehabilitation, to quantify long-term changes and treatment effects. Further, the process of rehabilitation will be looked at very closely regarding goal setting and attainment. Patients‘ and therapists‘ satisfaction with the rehabilitation progress will be requested on a regular weekly basis. From the close observation of the rehabilitation process we expect to get a deeper understanding of the needs of our patients and a basis to improve the treatment concept if necessary.

## Methods

### Ethics approval and consent to participate

The study is approved by the ethics committee of Rheinland-Pfalz, Mainz, Germany. We ask potential participants for written consent prior to their inclusion in the study.

### Participants

The participants are admitted to the two burn rehabilitation centers in Germany dependent on proximity to their place of residence and availability of a contemporary treatment capacity. Preliminary analyses revealed an overall similarity between the both programs except for small differences: The rehabilitation program in center A contains more occupational therapy; at center B the program contains additional balneotherapy, which involves treatment of the skin by bathing in natural mineral water. Center A is located at the campus of a level 1 trauma center, whereas center B is located in a health resort. The duration of the rehabilitation is planned for 3 weeks in both facilities and can be extended individually.

Only patients of the two burn rehabilitation centers who are insured by workers’ compensation (*Deutsche Gesetzliche Unfallversicherung*) are asked to participate in this study to avoid outcome bias by insurance status. This approach is described in other studies for work-related burn injuries [11] or other orthopedic injuries [17]. This effect is described in terms of satisfaction, pain, functional measures, return to work rate, and adverse events [18].

To start a rehabilitation program, the acute treatment must be completed, and no surgical interventions should be planned during the rehabilitation period. Mostly stable skin and scar conditions are essential to initiate a multimodal treatment to support scar maturing. In case of residual defects, healing under conservative treatment should be expected within a short time. An additional requirement is a sufficient cardio-pulmonary exercise capacity. Table 2 presents the inclusion and exclusion criteria for the study.

**Table 2 Tab2:** Inclusion and exclusion criteria for the present study

Inclusion criteria	Written consent
	Sufficient knowledge of German in speech and writing
	Age ≥ 18 years Work-related accident
Exclusion criteria	Serious cognitive impairment (e.g., advanced dementia, acute psychosis, traumatic brain injury)
	Declining of the study

Data will be collected on prepared case report forms (CRFs) and by questionnaires and will be entered continuously into an Access database.

### Interventions

No interventions besides the standard rehabilitation program in both centers are planned.

### Objective

The aim of the study is to evaluate the newly established rehabilitation concept in terms of pre-post comparison and through analyzing the rehabilitation process in matters of patients’ satisfaction with goal attainment.

#### Primary research question

Do the patients benefit from the rehabilitation program regarding their physical and psychological health conditions? Furthermore, are the changes steady after rehabilitation?

##### Hypotheses

The alternative hypothesis (H1) is as follows:
Physical and psychological outcome measures are enhanced after burn rehabilitation compared to measures before rehabilitation.Physical and psychological outcome measures are enhanced 3 and 12 months after rehabilitation compared to measures before rehabilitation.

The null hypothesis (H0) is as follows:
Physical and psychological measurements are not improved after the burn rehabilitation compared to measures before rehabilitation.Physical and psychological outcome measures are not enhanced 3 and 12 months after rehabilitation compared to measures before rehabilitation.

#### Secondary research questions I and II

##### Secondary research question I

Are there any differences regarding the effect of the rehabilitation treatment on the outcome measures between the two centers (non-inferiority of center A to center B)?

##### Secondary research question II

What are the most common rehabilitation goals of the patients, and to which ICF categories are they primarily linked? How do goals change during the course of rehabilitation? And how satisfied are the patients’ with their goal attainment?

### Design

This study uses a quasi-experimental prospective longitudinal design, including treating patients at two burn rehabilitation centers in Germany. For ethical reasons, randomization of patients or treatments is not possible; therefore, we added the non-inferiority question (comparison of the two centers). No intervention besides the standard rehabilitation program in both centers is planned. Participants will be screened at admission, at discharge, and at follow-up 3 and 12 months after discharge.

## Outcomes

### Initial patient characteristics

The patient demographics measured include age, gender, race/ethnicity, family status, and employment status. Medical characteristics include diagnosis and therapies, total body surface area (TBSA), partial thickness and full thickness burns, Abbreviated Burn Severity Index (ABSI), inhalation trauma, pneumonia or sepsis, other diagnoses, and therapies.

### Outcome measures

The types of outcome measures used to collect participant data are listed in Table 3.

**Table 3 Tab3:** Data collected at baseline (T1) and follow-up

	T1 Admission	Weekly	T2 Discharge	T3 3 months after discharge	T4 12 months after discharge
Physical outcome measures					
PWC 150	X		X	X	X
VSS	X		X	X	X
ROM of the large joints	X		X	X	X
Cutometer	X		X	X	X
Grip strength	X		X	X	X
DASH	X		X	X	X
Muscle function	X		X	X	X
LEFS	X		X	X	X
Psychological outcome measures					
BSHS-B	X		X	X	X
SF-36	X		X	X	X
IES-R	X		X	X	X
SCL-K-9	X		X	X	X
F-SozU	X		X	X	X
CSQ-8			X	X	X
ICF-based rehabilitation goals	X	X			
Semi-structured interview			X		

*PWC* physical working capacity test, *VSS* Vancouver Scar Scale, *ROM* range of motion, *DASH* Disabilities of the Arm, Shoulder and Hand, *LEFS* Lower Extremity Functional Scale, *BSHS-B* Burn Specific Health Scale-Brief, *SF-36* Short Form Health Survey, *IES-R* Impact of Event Scale-Revised, *SCL-K-9* Symptom Checklist 9, *F-SozU* Freiburg Social Support Questionnaire, *CSQ-8* Patient/Client Satisfaction Questionnaire, *ICF* International Classification of Functioning, Disability and Health

#### Physical outcome measurements

##### Physical fitness

General physical capacity is measured by the physical working capacity test 150 (PWC 150). The participant sits on a bicycle ergometer (Ergo-Fit Cardio Line 3000; Sport-Tec Physio & Fitness, Pirmasens, Germany). Heart rate is measured with a heart rate monitor with chest strap (Sigma Model Classic; Sigma-Elektro, Neustadt/Weinstraße, Germany) and will be recorded before, during, and after the test. The participant should reach a pedal-revolution rate of 70 rounds per minute (rpm). The exercise test begins with a workload of 25 watts (W), and the software automatically increases the workload by 25 W every 2 min. The target heart rate (beats/min) is calculated as 150 minus the age of the participant. When the individual target heart rate has been exceeded for more than 30 s, the final workload stage is reached and will be recorded. After this stage, a 5-min recovery period at 25 W will follow in which the heart rate recovery is recorded. The applied termination criteria are decreasing heart rate despite increasing exertion (for more than 30 s), chest pain or a feeling of constriction in the chest, shortness of breath, headache, dizziness, subjective exhaustion, leg fatigue, leg cramps, and a pedal-revolution rate below 60 rpm.

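### The PWC 150 target heart rate of 150 minus age does not sit with the test's name and gives low targets at older ages, which risks a first-stage floor and reduced sensitivity to change

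*Protocol article*

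**What the plan says.** All of the test rules are in the protocol article under Physical fitness.

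- **Target:** "The target heart rate (beats/min) is calculated as 150 minus the age of the participant".
- **Load:** "The exercise test begins with a workload of 25 watts (W), and the software automatically increases the workload by 25 W every 2 min".
- **Result:** "When the individual target heart rate has been exceeded for more than 30 s, the final workload stage is reached and will be recorded".
- **Other data:** heart rate "will be recorded before, during, and after the test", followed by "a 5-min recovery period at 25 W will follow in which the heart rate recovery is recorded".

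Table 3 lists PWC 150 among the physical outcomes at admission, discharge, 3 months and 12 months. Under Statistical methods, the outcome measures are compared between T1 and T2, T1 and T3, and T1 and T4 by paired one-sided t tests.

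Table 2 admits adults with no upper age limit ("Age ≥ 18 years Work-related accident"), and Table 1 lists age above 50 as a further indication for burn rehabilitation. Older patients are therefore expected in the sample.

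**The concern.** The end-point rule decides what number the fitness outcome takes. Two features of it raise doubt.

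First, the number 150 in the test name never appears as a target for any eligible patient, because age is always subtracted. Either the name, the formula or the condensing of the full protocol may be at fault, and a reader cannot tell which test the centres run.

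Second, the stated target falls by one beat for each year of age, while the lowest recordable result stays at 25 W. If a patient's heart rate at 25 W already exceeds the target, the result is 25 W. If this happens at both compared visits, any gain between them is lost. PWC 150 is the article's measure of general physical capacity under the primary research question, so a floor there would understate benefit in older patients.

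**Working it through.** **Step 1. Targets from the stated rule (no assumption needed).** Target = 150 − age: 132 at age 18, 120 at 30, 110 at 40, 100 at 50, 90 at 60 and 85 at 65.

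**Step 2. Margin over the starting rate (assumed, since the documents give none).** Margin = 150 − age − starting rate.

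| Age | Start 70 | Start 80 | Start 90 |
|---|---|---|---|
| 40 | 40 | 30 | 20 |
| 50 | 30 | 20 | 10 |
| 60 | 20 | 10 | 0 |

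**Step 3. Recorded stage in single cases.** The model is heart rate = starting rate + k for each 25 W. The recorded stage is the first one at which heart rate exceeds the target.

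- Start 80, k = 12, age 60 (target 90): 92 at 25 W, so 25 W is recorded.
- Same patient at age 40 (target 110): 92, 104, 116, so 75 W is recorded.
- Improvement from (80, 12) to (75, 10) at age 60: 85 at 25 W and 95 at 50 W, so the result moves from 25 W to 50 W and the gain registers.
- Improvement from (90, 15) to (85, 12) at age 60: 105 before and 97 after at 25 W, both above 90. The result stays at 25 W and the gain is lost.
- The same improvement at age 50 (target 100): 105 before, then 97 and 109 after, so the result moves from 25 W to 50 W.

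A patient on the floor can therefore still move up. A gain is wholly hidden there only when heart rate at 25 W exceeds the target at both visits.

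**Step 4. Population range by simulation.** Assumptions, none of them in the documents: pre-load rate normal with SD 12 and the mean shown, slope normal with mean 0.5 and SD 0.1 beats/min per watt, age uniform on 20 to 62. The workload at the target is (150 − age − pre-load rate) / slope, and the recorded value is the 25 W stage in which it falls, at least 25 W. The improvement is 5 beats/min lower at every load, a true gain of 5 / slope, which averages 10.46 W.

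| Mean pre-load rate | First stage, all | First stage, age ≥ 50 | Recorded / true gain, all | Recorded / true gain, age ≥ 50 |
|---|---|---|---|---|
| 70 | 6% | 18% | 10.31 / 10.46 = 99% | 9.96 / 10.46 = 95% |
| 80 | 18% | 45% | 9.78 / 10.46 = 93% | 8.45 / 10.46 = 81% |
| 88 | 32% | 70% | 8.80 / 10.46 = 84% | 6.07 / 10.46 = 58% |

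A flatter heart-rate response shrinks the floor further. With a slope of 0.35 and a pre-load rate of 70, the first-stage shares are 4% overall and 12% at age 50 or over.

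**Step 5. Separating the floor from the rounding.** At a pre-load rate of 88, the 5 beats/min improvement leaves the stage unchanged in 65% of all patients, but also in 62% of those who are not on the floor. Most of that share is the 25 W step, which exceeds the average 10.46 W gain, and would arise under any target. The floor is what lowers the mean gain in Step 4.

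**The case against.** **The name is not shown to be contradicted.** A reader might infer a strict contradiction between PWC 150 and an age-adjusted target. The article never says what 150 stands for, and the number occurs in both the name and the formula. A fixed target of 150 would have to be imported from outside knowledge of the test. The full protocol (version 7.0) is not shown, and a slip in condensing it is possible. This stands: the mismatch is one of appearance, and the remedy is reconciliation.

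**The outcome can still register improvement.** A reader might infer that it cannot, or that older patients score 25 W at every visit. Neither follows. Younger adults mostly have several stages of room. Even at a pre-load rate of 88, 21% of first-stage patients aged 50 or over move up after a 5 beats/min improvement. Rounding to 25 W largely averages out in the mean that the paired t test uses. This stands too.

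**The size rests on assumed heart rates.** It does, and the article also requires sufficient cardio-pulmonary capacity to start rehabilitation, which may favour the milder end. That is why a range is given.

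**The consequence is limited.** PWC 150 is one of many outcomes, none is designated primary, and the sample size is not based on it. A reader might also infer a distorted comparison between centres, but no age difference is documented and age is a matching variable. How a test stopped early for fatigue or exhaustion is scored is detail that an article may leave to the full protocol, so it is not part of this point.

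**Other heart-rate data are collected.** This is true and makes the fix cheap. It does not remove the issue, because the recorded workload result is still the stage. For a patient who ends in the first stage, the recovery load of 25 W equals the load that ended the test.

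**Conclusion.** The point holds in a limited form. As printed, the rule never gives 150 for an eligible adult and produces low targets at older ages. Combined with a 25 W start and 25 W steps, it puts some older patients at risk of a floor and lowers sensitivity to change. The targets are certain from the text. The extent is not: 6% to 32% of all patients and 18% to 70% of those aged 50 or over ending in the first stage depends on assumed pre-load rates of 70 to 88, a slope of 0.5 and ages 20 to 62, and a flatter slope gives less. Over that range the mean recorded gain is attenuated slightly to moderately overall (84% to 99% retained), and more at age 50 or over (58% to 95%). The bias is towards understating improvement. This should be fixed, but the documents do not support treating the outcome as unusable.

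**What to change.** 1. Check the test name and the target formula against the full protocol and the program on the ergometers, without presuming which is right. Correct the text, and use one confirmed rule at both centres and all four visits.
2. Analyse an interpolated workload instead of the 25 W stage alone. For a reference heart rate HR* lying between two recorded loads: workload = lower load + (load difference) × (HR* − HR at lower load) / (HR at higher load − HR at lower load). Choose HR* for each patient as a rate reached at all the visits being compared.
3. Derive tests already performed in the same way, and report at each visit how many ended in the first stage.

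**Cost:** a wording correction and extra derivation from heart rates that the article says are already recorded, with no new visits or equipment. Interpolation helps least where the floor bites: a patient who ended in the first stage has only a pre-load rate and rates at 25 W, and so yields only a low-intensity value. The count in item 3 shows how much that matters.

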##### Grip strength

Grip strength will be measured with a Jamar dynamometer (Sammons Preston Inc., Bolinbrook, IL, USA) at level 2. The participant will sit in front of the rater, holding the elbows close to the body and flexed at 90 degrees with the wrists in a neutral position. The participant will be requested to press the dynamometer with maximum force. Three trials with each hand will be carried out [19].

##### Muscle function test

Major muscle function is tested according to Janda [20]. Muscles of the upper and lower extremities are tested by a skilled physiotherapist, rating the muscle functioning from 0 = “no contraction” to 5 = “normal functioning.”

##### Burn scar assessment

Burn scars will be assessed at two representative sites using the Vancouver Scar Scale (VSS) and cutometry. Both sites are selected by the examiner as representative and are documented by an anatomical description of the location and by photo documentation to ensure retrieval of exactly the same spot in the follow-up measures.

The VSS will be used to clinically evaluate the burn scar formation and characteristics. The VSS assesses four parameters of the scar, including vascularization, pigmentation, pliability, and height/thickness, giving a range of 0–14 in the total score. The appearance of the burn scar will be evaluated by a physician [21].

Properties of the scar will be measured objectively with the Cutometer® Multi Probe Adapter (MPA) 580 (Courage + Khazaka electronic GmbH, Cologne, Germany). The Cutometer® MPA 580 is a device that measures the firmness and elasticity of skin. A negative pressure is created with a vacuum, the skin is drawn into the aperture of the probe, and after a defined time it is released. Inside the probe, the height of skin that is drawn up is determined by a non-contact optical measuring system. The resistance of the skin to the negative pressure (firmness) and its ability to return to its original position (elasticity) are displayed as curves (penetration depth in millimeters/time), and parameters (R0 and R2) are calculated [22].

##### Burn contracture

The extent of burn contracture of the large joints will be measured by range of motion (ROM) using a standard goniometer.

##### Self-reporting questionnaires

Two questionnaires are used. The Disabilities of the Arm, Shoulder and Hand (DASH, German version [23]) questionnaire is a 30-item self-report outcome measurement for physical function and symptoms in patients with one or multiple musculoskeletal disorders of the upper limb. In addition to the Disability/Symptom module (30 items, scored 1–5), the DASH contains two optional modules: Sports/Performing Arts and Work (each scale consists of four items, scored 1–5). Each score is converted to a 0–100 scale. Higher scores indicate greater disability. The DASH is widely used and has demonstrated its clinical value for several different medical conditions of the upper limb.

The Lower Extremity Functional Scale questionnaire for patients with foot and/or leg injuries (LEFS [24]) is a 20-item condition-specific functional status measure applicable to a wide spectrum of patients with lower extremity conditions of musculoskeletal origin. Each LEFS item is scored on a Likert scale from 0 to 4, with higher scores representing higher functional levels; the maximum score is 80. Normative data are available for comparison.

#### Psychological outcome measurements

##### Burn Specific Health Scale-Brief questionnaire (BSHS-B, German version [25])

The BSHS-B measures the most important domains of a patient’s quality of life that are affected after burn injury. The BSHS-B consists of 40 items divided into 9 different subscales: affect, interpersonal relationships, sexuality, simple abilities, hand function, work, heat sensitivity, treatment regimens, and body image. Each item asks about the extent of a specific limitation and can be answered on a 5-point Likert scale that ranges from 0 = “extremely limited” to 5 = “not limited at all.” The higher the score, the lower the perceived impairment.

##### Short Form Health Survey (SF-36, German version [26])

The SF-36 questionnaire is one of the most commonly used assessments to measure an adult person’s perceived physical and mental health-related general quality of life. The questionnaire includes eight scales; four can be summarized into the General Mental Health scale, while the remaining four domains form the General Physical Health scale. All subdomains are assessed using a 5-point Likert scale (except Physical Functioning, which is evaluated using only a 3-point scale). The scores are converted to a 0–100 scale. The higher the score, the higher the perceived quality of life.

##### Symptom Checklist-9 (SCL-K-9 [27])

The original Symptom Checklist-90-Revised (SCL-90-R) is a widely used questionnaire developed to determine a number of psychological symptoms. Its shortened version has shown equally high internal consistencies as a suitable screening instrument to assess a wide range of psychopathologic symptoms. The questionnaire contains one-dimensional items which are scored on a 4-point Likert scale ranging from 1 (“not at all”) to 4 (“extremely”).

##### Impact of Event Scale-Revised (IES-R [28])

The IES-R is a 22-item, self-report questionnaire that assesses post-traumatic stress symptoms in relation to a specific event. It is one of the most commonly used metrics of post-traumatic stress disorder (PTSD) symptomatology. Items are rated on a 5-point scale ranging from 0 (“not at all”) to 4 („extremely”).

##### Recording perceived social support (F-SozU-14 [29])

A person’s perceived social support will be measured with the short version of the Freiburg Social Support Questionnaire (F-SozU-14), a 14-item questionnaire comprising emotional and practical support as well as social integration and social burdens. The items are rated on a 5-point Likert scale, ranging from 1 (“does not apply”) to 5 (“exactly applicable”).

